### Statistical methods

Data are entered via special MS Access entry masks automatically controlling for data plausibility. In addition, sections of entered data are checked for typing errors by hand, in order to ensure an error rate lower than 0.2%. Baseline measures and demographics of participants significantly differing at baseline in intervention and control group and control measures are used as co-variates in an analysis of variance with repeated measures with two groups and four measurement time points. If the diagnosis of extent and type of missing data reveal that the precondition is given, the Full Information Maximum Likelihood (FIML) method will be applied for data replacement [73]. The primary intention-to-treat analysis, including all participants with valid data (whether they did or did not receive the intervention), will be compared with a per protocol analysis excluding all participants with documented deviations from the protocol (ie. not receiving the entire intervention or receiving an incomplete follow-up). The comparison of these groups will be adjusted for baseline imbalance and process variations. Variations in the adherence to protocol; to the treatment manual and to therapeutic recommendations; variations in medication and progress of cognitive decline as well as variations in the quality of supporting or hindering structures and processes at the study sites are considered as possible mediators. All statistical tests will be two-sided on an alpha level of .05.

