### Outcomes

The primary endpoint is the comparison between the intervention group and control group in the change in daily functioning from baseline to follow-up as indicated by the Interview for Deterioration in Daily Living Activities in Dementia (IDDD) over three post intervention time points. The WHEDA measurement scheme with dependent variables and measurement instruments is provided in table 1. The primary and most secondary outcomes are oriented to patient and caregiver. Daily functioning, quality of life, mood and daily interaction are directly related to individual everyday life and represent the user's perspective in most self- and proxy-assessments used in the WHEDA study. It is of great importance to know how long a therapeutic approach may stabilise daily functioning after the intervention is finished. The cognitive decline in dementia is a strain on patients and caregivers. Its progress varies, but major and consistent changes are mostly not observable before a half year progress of disease. Consequently, the follow-up assessments are appointed at week 16 and 26 after baseline. In order to justify a potential implementation in practice, service providers as well as political and economical decision-makers within the health care system need trustworthy evidence about an innovative intervention. Hence feasibility, acceptance and costs of active and control treatment are additional outcomes of the WHEDA study.

**Table 1 T1:** WHEDA measurement scheme

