#### Control measures

• The Sociodemographic Questionnaire provides data on the patient's and primary caregiver's age, sex, socio-economic and educational status, relation between patient and caregiver and their housing. It is a self- and proxy-report of the primary caregiver.

• The study physician evaluates the patient's cognitive status using the Mini Mental State Examination, a broadly applied performance test with established metric properties [32]. The MMSE ranges from 0 to 30. The higher the score the better the cognitive status.

• The Geriatric Depression Scale (GDS [71]) is a self-rating scale consisting of 30 questions to be answered dichotomously as 'yes' and 'no'. The GDS score ranges from 0 to 30; higher scores indicate major depressive indicators. The cut-off point for depression is 12. Correlation of GDS and CSDD scores was .70 in a German sample of 140 patients with mild dementia [65]. The authors found sufficient internal consistency in subgroups of patients with mild (MMSE ≥ 18) and moderate to severe (MMSE<18) dementia (Cronbach's alpha: .83, .74 respectively).

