### Sample size

Although the Dutch original randomised control trial [26] found very large effect sizes on the performance scale of the Interview of Deterioration in Daily Living Activities in Dementia (at 12 weeks follow-up d-value = 2.4), the power of the WHEDA-study is calculated conservatively in order to detect small effects. The rationale is the change in design; that there is an active control treatment, less professional experience in the experimental treatment in Germany, less patients per therapist and a longer follow-up in a sample with expected progress in dementia, may reduce the expected effects. The power calculation is based on an analysis of variance of two groups and four measurement time points (since in the postal follow up at 52 weeks the IDDD is recorded, too). Hypothesising an alpha of .05 (two-sided), a power of .80 and a correlation of .7 between four measurement time points, a sample of 84 persons is needed, in order to detect an effect of f = .10 [72]. According to drop out rates of the Dutch study, 280 patients must be screened and 140 recruited (see figure 1).

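### Part of the covariate set for the repeated-measures analysis is chosen by significance tests of baseline differences between randomised arms, so it is data-driven and not fixed in advance

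*Protocol article*

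**What the plan says.** The Statistical methods section describes one model and draws its covariates from two sources.

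- The first source is "Baseline measures and demographics of participants significantly differing at baseline in intervention and control group", so entry depends on a between-arm test. No separate threshold is given. The section sets .05 two-sided for all tests, and I take that to apply here.
- The second source follows in the same sentence: "control measures are used as co-variates in an analysis of variance with repeated measures with two groups and four measurement time points". On the natural reading this set carries no significance condition. The Control measures section and Table 1 list its members: sociodemographic data, GDS and MMSE, and (in the table only) medication and periods of illness.

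Demographics belong to both sources. They are named in the first, and the Control measures section also lists them: "The Sociodemographic Questionnaire provides data on the patient's and primary caregiver's age, sex, socio-economic and educational status".

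The primary endpoint in the Outcomes section is the between-group comparison of "change in daily functioning from baseline to follow-up as indicated by the Interview for Deterioration in Daily Living Activities in Dementia (IDDD"), over three post-intervention time points. Table 1 marks the IDDD at weeks 0, 6, 16 and 26. The Sample size section assumes "a correlation of .7 between four measurement time points".

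**The concern.** Allocation is computer-generated and 1:1, so a significant baseline difference between arms is a chance event. Testing for it says nothing about whether the variable predicts daily functioning. The screen therefore admits variables at random and can pass over strong predictors.

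Three things are at stake. First, the adjustment set for the primary comparison is unknown until baseline data have been compared by arm, so the estimate and its standard error depend on a preliminary test. Second, demographics have two conflicting entry rules. Third, on the plan's own correlation baseline IDDD is a strong predictor, but it is used as a covariate only when the arms happen to differ on it. It would then serve both as a covariate and as the first repeated outcome.

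**Working it through.** **Inputs from the protocol article.** Sample size: alpha .05 two-sided, power .80, correlation .7, four measurements, f = .10, N = 84. Statistical methods: .05 for all tests. Outcomes and Table 1: baseline plus three post-intervention IDDD scores.

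**Assumptions of this check.** Compound symmetry, SD 1 at each visit, a constant shift d at all three post-intervention visits, 42 patients per arm, independent candidate covariates, and a baseline-by-time term fitted whenever baseline is a covariate.

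**1. The plan's own figure.** For the group-by-time interaction, lambda = f² × N × m / (1 − rho) = .01 × 84 × 4 / .3 = 11.2, with 3 and (84 − 2) × 3 = 246 degrees of freedom. Power is .805, and 84 is the smallest even N that reaches .80. The figure reproduces.

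**2. How the screen behaves.** One variable is selected with probability .05 (simulated: .049). With K candidates, the chance that at least one enters is 1 − .95^K:

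| K (assumed) | Chance that at least one enters |
|---|---|
| 5 | 23% |
| 10 | 40% |
| 20 | 64% |

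**3. Residual variance for the mean of the three post-intervention scores.**
- Variance of that mean: (1 + 2 × .7)/3 = .80.
- Change from baseline: .80 + 1 − 2 × .7 = .40.
- Baseline always a covariate: .80 − .7² = .31.
- Ratio: .40/.31 = 1.29, so the change-type analysis needs about 29% more patients for equal precision.

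**4. Linking d to the plan's f.** With group differences of 0, d, d, d over the four visits, the interaction effects per arm are ±.375d once and ±.125d three times. Hence f = d × √[(.375² + 3 × .125²)/4] = .2165d. So d = .46 gives f = .0996, the plan's effect, and d = .34 gives f = .074, a smaller effect than planned.

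**5. Power at N = 84 for the single-degree-of-freedom contrast.** The standard error is √(variance × 2/42): .138 for change and .1215 with baseline as covariate. Dividing d by these gives 2.46 and 2.80 at d = .34, and 3.33 and 3.79 at d = .46, against a critical value of about 1.99.

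| d | Change, closed form | Change plus the screen, simulated | Baseline always a covariate, closed form / simulated |
|---|---|---|---|
| .34 | 68% | 68.9% | 79% / 78.4% |
| .46 | 91% | 91.6% | 96% / 96.2% |

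The 91% exceeds the plan's 80% at the same effect because this contrast has one degree of freedom and the interaction test has three.

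**6. Type I error.** Change plus the screen, 20,000 simulated trials with no effect: .045.

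**7. When baseline IDDD is selected.** It reaches p < .05 at an imbalance of about 1.99 × √(2/42) = .43 SD. There the change and covariate-adjusted estimates differ by (1 − .7) × .43 = .13 SD.

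**The case against.** The strongest defence is that the analysis is valid and less exposed than the quoted phrase suggests. Most of this stands.

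- **Not every covariate is screened.** A reader might infer that nothing enters without a significant imbalance. The same sentence adds control measures with no such condition, so baseline cognition and depression appear to be adjusted for in any case. What remains is the screened set and the double listing of demographics.
- **Baseline IDDD is not left out of the model.** A reader might infer that it is, and compare a post-only analysis with one adjusted for baseline. At an assumed shift of .35 SD that gives 44% power against 81%, and a type I error of 3.1%. The documents do not support this comparison. The endpoint is change from baseline, and Table 1 makes week 0 the first of the four measurements. With baseline kept in as change, the same shift gives 72% against 81%.
- **The week-52 remark.** The Sample size section explains its four time points by a postal IDDD at week 52. That could suggest four post-baseline scores, but it conflicts with the three post-intervention time points in Outcomes and with Table 1, which marks no IDDD at week 52. It is a reason to state the role of baseline clearly, not evidence that baseline is omitted.
- **Change-based repeated measures is legitimate in a randomised trial**, and double use of baseline IDDD would arise in only about 5% of trials. Both points are fair. Neither justifies choosing the other covariates by a test of chance differences.

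**Conclusion.** The point holds in a limited form. The article states a rule that selects baseline measures and demographics by between-arm significance. This is an explicit choice, not a detail left to an analysis plan. It leaves part of the primary adjustment set to chance, ignores prognostic strength and gives demographics two entry rules.

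The statistical cost is moderate. At the planned effect it is about 5 percentage points of power (91-92% against 96%), and at .34 SD about 10 points (69% against 78%). The false-positive rate is not raised. The main harm is incomplete pre-specification, with some loss of precision from a score already scheduled at baseline.

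The sizes rest on the plan's correlation of .7 with compound symmetry, a constant post-intervention shift and 84 analysed patients. The shifts of .34 and .46 SD are assumptions of this check, the second chosen to match f = .10. The number of candidate covariates is also assumed.

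**What to change.** 1. Delete the significance screen.
2. Name the covariates in advance on prognostic grounds: baseline IDDD Performance score, week −1 MMSE, and centre, by which randomisation was blocked. State a single rule for demographics.
3. Analyse the IDDD at weeks 6, 16 and 26 as the repeated outcomes, with baseline IDDD as a covariate only, so that it is never used twice.
4. Label adjustment for any other chance imbalance as a sensitivity analysis.

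This costs wording only, needs no new data, and should be settled before outcomes are compared by arm. The one downside is small: a chance imbalance in a variable not on the list is handled only in the sensitivity analysis.

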#### Secondary outcomes

• To evaluate the effectiveness of the COTP on patients' and caregivers' quality of life, mood and satisfaction with treatment and on caregivers' sense of competence and hours of care compared to those having a COTC.

• To evaluate the cost of both interventions from a societal perspective.

The intervention group receives ten sessions of occupational therapy during five weeks of one hour duration. The control group receives one home consultation of one hour duration by an occupational therapist within the same period. Measurements for both groups are at baseline before intervention (week 0), after intervention (week 6) and at follow-up (week 16, 26 and 52). Measurements of cognitive decline are applied one week before baseline and at week 11 and week 21 after baseline.

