**Control measures**												
Demographic data	Socio-demographic questionnaire		X									
Depression	GDS	X										
Cognition	MMSE	X			X		X					
Medication	Adapted RUD (+ diary as reminder)		X	X	X	X	X	X	X	X	X	X
Periods of illness	Adapted RUD (+ diary as reminder)		X	X	X	X	X	X	X	X	X	X

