• The primary caregiver provides data on his/her own and the patient's resource utilization in a self- and proxy-report (adapted Resource Utilization in Dementia RUD [68]). The adapted RUD records resource utilization in the following fields:

 a. Medical care for the patient: (1) periods of illness, nights in hospital or nursing home, number of consultations and purchase of technical aids within the last six weeks. (2) Number and duration of therapy sessions (such as physical or psychotherapy), nursing care or home care and visits to day care groups within the last two weeks;

 b. Informal care for the patient: (1) Hours per day of the primary caregiver for assistance in activities of daily living, instrumental activities of daily living and supervision; and also hours per day the patient is without supervision. (2) Hours of supervision by others, informal or professional caregivers within the last two weeks (as recommended by Neubauer et al. [69]);

 c. Medication of the patient within the last two weeks;

 d. Medical care for the caregiver: (1) periods of illness, nights in hospital or nursing home, number of consultations and purchase of technical aids within the last six weeks. (2) Number and duration of therapy sessions, nursing care or home care, visits to groups for caregivers of people with dementia within the last two weeks;

 e. Amount of work per week and days absence from work of the primary caregiver;

 f. Medication taken by the primary caregiver within the last two weeks.

Wimo and Nordberg [70] found fair to high correlations between times of caregiving as observed by a special team and estimated in RUD by the caregivers in twenty institutionalized persons with dementia (correlation coefficients in ADL-time .81, *p *< .001; in IADL .29, *p *= .03; supervision .51, *p *< .001). In the WHEDA-study, the adapted RUD is applied at every measurement time point after recruitment, in order to record the full resource utilization until the one year follow up. For supporting the retrospective data collection, the caregiver keeps a diary of periods of illness, nights in hospital or nursing home, number of consultations and purchase of technical aids.

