#### Process measures

• Problems during treatment and adherence to the manuals are recorded by an evaluation form for every treatment case in both study groups.

• The study therapists evaluate their adherence to the study protocol as well as barriers and facilitators of the treatment process within a self-report questionnaire for the relevant period (seminar, pilot phase, treatment series). In addition, this questionnaire collects the therapists' ratings and comments on the adherence of patients and caregivers to therapeutic recommendations (interventions group only, since follow up visits are missing in control group and control for adherence is not possible). The summarised self-report results are reflected in a focus group discussion for all therapists involved in the study.

• Further indicators of adherence to protocol are the numbers of treatments, assessments and medical control visits inside, versus outside, the protocol schedule. Additionally, the completeness of measurements at every time point is evaluated (eg. videotape or patient interview might be missing due to reduced cognitive capacity).

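### The covariate rule for the primary repeated-measures model does not restrict control measures to baseline values, so as written it admits post-randomisation variables that treatment may affect

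*Protocol article*

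**What the plan says.** The Statistical methods section of the protocol article defines two groups of covariates. The first is baseline measures and demographics on which the arms differ significantly at baseline. The second is the control measures. The sentence runs: "in intervention and control group and control measures are used as co-variates in an analysis of variance with repeated measures". The reference to baseline belongs to the first group only.

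Table 1 has a block headed control measures with five rows: demographics, GDS, MMSE, medication, and the row "Periods of illness". On MMSE, the Design section says: "Measurements of cognitive decline are applied one week before baseline and at week 11 and week 21 after baseline". Medication and illness come from the resource-use questionnaire (RUD), and the Secondary outcome measure section says that "the adapted RUD is applied at every measurement time point after recruitment".

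Three further statements in Statistical methods bear on the point:

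- The population: "The primary intention-to-treat analysis, including all participants with valid data (whether they did or did not receive the intervention").
- After the sentence setting this analysis beside a per-protocol analysis: "The comparison of these groups will be adjusted for baseline imbalance and process variations".
- Among the possible mediators: "variations in medication and progress of cognitive decline as well as variations in the quality of supporting or hindering structures and processes".

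Under Process measures, therapists' ratings of how well patients and caregivers followed recommendations are collected for the "interventions group only, since follow up visits are missing in control group and control for adherence is not possible".

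**The concern.** Randomisation makes the arms comparable on everything fixed beforehand. It does not do so for variables that arise afterwards. If COTP changes such a variable, holding it constant removes the part of the effect that runs through it. It can also open a non-causal path if the variable and the outcome share an unmeasured cause. The adjusted contrast is then no longer the effect of being allocated to COTP rather than COTC, which is what the primary endpoint is meant to capture. Calling the analysis intention-to-treat does not help, because that label fixes who is analysed and not what is conditioned on.

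The article gives its own grounds for caution. It names medication and cognitive decline as possible mediators, and the Abstract counts medication, through the caregiver's diary, among the secondary outcomes.

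**Working it through.** **1. Which control measures post-date randomisation (Table 1)**

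| Control measure | Weeks | Follow-up values |
|---|---|---|
| Demographics | 0 | none |
| GDS | -1 | none |
| MMSE | -1, 11, 21 | 2 of 3 |
| Medication | 0, 6, 11, 16, 21, 26, 32, 38, 45, 52 | 9 of 10 |
| Periods of illness | same ten weeks | 9 of 10 |

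Three of the five have follow-up values. Table 1 schedules the IDDD at weeks 0, 6, 16 and 26. MMSE at week 11 therefore comes after the week 6 outcome, and MMSE at week 21 comes after the week 6 and week 16 outcomes. Four of the nine follow-up medication and illness records (weeks 32 to 52) come after the last IDDD visit in the table.

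**2. The plan's own figure**

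Inputs from Sample size: f = 0.10, correlation 0.7, four time points, two groups, alpha 0.05, power 0.80. For the group-by-time interaction:

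- noncentrality = N × f² × m / (1 − rho) = 84 × 0.01 × 4 / 0.3 = 11.2
- degrees of freedom = 3 and (84 − 2) × 3 = 246
- power = 0.805, so N = 84 is reproduced
- 84 / (1 − 0.40) = 140; the 40% loss is implied by the two figures and not stated

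The calculation contains no covariates, so changing the covariate rule leaves N as it is.

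**3. Conditioning at a single visit**

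Let treatment shift the covariate by a (in SD), and let s be the within-arm slope of outcome on covariate. Then

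adjusted effect = total effect − a × s.

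The article gives neither a nor s. As an illustration, assume a total effect of 0.30. With no shared cause, s = b, the direct slope. With an unmeasured cause loading 0.4 on both variables, s = b + 0.4² = b + 0.16.

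| a | b | No shared cause | Shared cause |
|---|---|---|---|
| 0 | 0.3 or 0.5 | 0.30 | 0.30 |
| 0.2 | 0.3 | 0.24 | 0.21 |
| 0.2 | 0.5 | 0.20 | 0.17 |
| 0.4 | 0.3 | 0.18 | 0.12 |
| 0.4 | 0.5 | 0.10 | 0.04 |

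A simulation with 400,000 subjects per case agrees to within about 0.01. If a and s have opposite signs, adjustment inflates the effect instead.

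**4. Conditioning when the endpoint is change from baseline**

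The Outcomes section defines the endpoint as change in IDDD from baseline. For a difference of zero at baseline and d at each of the three later visits, the interaction effect size is f = d × √3/8 = 0.2165d. So f = 0.10 corresponds to d = 0.10 / 0.2165 = 0.462 SD.

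For unit-variance variables, where r is the covariate–outcome correlation at a visit, adjustment moves the change contrast by a × (r at follow-up − r at baseline):

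- a = 0.2, r = 0.5 at both: 0.462 − 0.2 × 0 = 0.462
- a = 0.3, r = 0.6 at both: 0.462 − 0.3 × 0 = 0.462
- a = 0.3, r rising from 0.45 to 0.60: 0.462 − 0.3 × 0.15 = 0.417

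If baseline IDDD is instead a covariate, the slope on the follow-up variable is (r − 0.7r) / (1 − r²):

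- a = 0.2, r = 0.5: slope 0.15 / 0.75 = 0.20; 0.462 − 0.2 × 0.20 = 0.42
- a = 0.3, r = 0.6: slope 0.18 / 0.64 = 0.28; 0.462 − 0.3 × 0.28 = 0.38

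The possible shift therefore runs from nothing to something material, depending on unstated correlations and on how baseline enters the model.

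**The case against.** The strongest reply is that the article nowhere says follow-up values enter the primary model. The text section headed Control measures describes only the sociodemographic questionnaire, MMSE and GDS; medication and illness carry that label in Table 1 alone. The follow-up MMSE weeks coincide with no IDDD visit, which suits a baseline covariate better than a visit-matched one. Naming medication and cognitive decline as mediators could mean that their follow-up values are reserved for a separate analysis. An analysis plan that is not shown may settle the time points.

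Much of this stands. A reader might infer that the primary comparison definitely is adjusted for week 11 and week 21 MMSE and later medication; the text permits that but does not establish it. What remains is that the article states a rule, the rule has no time restriction, and the only table defining the term includes follow-up values. The rule can be followed to the letter and give a conditioned contrast.

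A reader might also infer that the primary contrast is adjusted for process variations. The documents do not support that as settled. The groups being compared in that sentence may be the intention-to-treat and per-protocol sets just mentioned, and the Discussion presents process-adjusted analyses as a way to explain differences from the Dutch trial. Likewise, nothing places the COTP-only adherence ratings in the two-arm model. Both points call for a clarifying sentence and no more.

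**Conclusion.** The point holds as a defect in a stated rule: the primary model's control-measure covariates are not limited to values fixed before randomisation, and some of the variables concerned are named as possible mediators in the same paragraph. Following the rule as written can bias the COTP versus COTC contrast. It is not shown that it will. Mediation bias requires that treatment shifts the covariate, and the article gives no evidence on whether COTP changes MMSE, medication or illness.

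No size or direction can be given from the document. A reader might multiply an assumed shift of 0.1 to 0.3 SD by an assumed correlation of 0.3 to 0.6, obtain 0.03 to 0.18 SD, and report 7% to 39% of 0.46 SD. That does not hold: the product is a shift in the level at one visit, whereas both the endpoint and the 0.46 SD benchmark concern change from baseline, for which the shift may be near zero. The figures in steps 3 and 4 of the working rest on assumed inputs and illustrate the mechanism only.

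**What to change.** Reword the covariate sentence so that the primary intention-to-treat model uses only pre-specified covariates whose values are fixed before randomisation, for example MMSE and GDS at week -1, demographics, baseline medication and centre. Include baseline IDDD as a covariate only if it is not also one of the four outcome time points. The article places week 0 before the intervention without stating its order relative to allocation, so confirm that order for any week 0 covariate.

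Then add three statements:

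- Follow-up MMSE, medication and periods of illness are used only in separately labelled exploratory mediation analyses.
- Adjustment for process variations belongs to the explanatory analyses and not to the primary contrast.
- The adherence ratings collected in the COTP arm alone are not a covariate in any two-arm model, since they have no counterpart under COTC.

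The cost is a few sentences. No new data are needed and the sample size stays at 84 evaluable and 140 recruited. If baseline values were always intended, one sentence saying so resolves the main issue.

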**Primary outcome**												
Patients' functioning in everyday life	IDDD, PRPP-Video rating		X	X		X		X				

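### If baseline IDDD is one of the four ANOVA time points, as the text best supports, baseline covariates entered without time interactions leave the group-by-time test unadjusted for baseline imbalance

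*Protocol article*

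**What the plan says.** All references are to the protocol article.

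- **Outcomes:** the primary endpoint is the between-arm comparison of "change in daily functioning from baseline to follow-up as indicated by the Interview for Deterioration in Daily Living Activities in Dementia (IDDD"), taken "over three post intervention time points".
- **Table 1:** the row "IDDD, PRPP-Video rating" has four marks, which line up with weeks 0, 6, 16 and 26. There is none at week 52.
- **Sample size:** the calculation assumes "two groups and four measurement time points (since in the postal follow up at 52 weeks the IDDD is recorded, too"). It uses "Hypothesising an alpha of .05 (two-sided), a power of .80 and a correlation of .7 between four measurement time points" and gives 84 persons for f = .10, with 140 to be recruited.
- **Statistical methods:** the covariates are "Baseline measures and demographics of participants significantly differing at baseline in intervention and control group and control measures"; they "are used as co-variates in an analysis of variance with repeated measures with two groups and four measurement time points". The section also states an intention to adjust for baseline imbalance. It does not say whether covariates enter as main effects only or also by time, and it does not name the effect tested.

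**The concern.** Choosing covariates because they differ at baseline shows that they are meant to protect the comparison from chance imbalance. In a repeated-measures ANOVA with baseline among the levels, the treatment effect on change is carried by group-by-time, which is built from within-patient contrasts. A value that is constant within a patient shifts all of that patient's visits equally and drops out of those contrasts. If baseline IDDD is the imbalanced variable, it would be both a covariate and the week-0 outcome.

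At stake is a report that says it adjusted for baseline when the primary test was unaffected. The arm that starts worse by chance tends to move back towards the mean, and this would be read as a treatment effect.

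**Working it through.** **1. Which test does 84 belong to?** Inputs from the Sample size section: k = 2 groups, m = 4 time points, f = .10, correlation ρ = .7, two-sided alpha .05, power .80.

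- Group-by-time: λ = f²·N·m/(1−ρ) = 0.01 × 84 × 4 / 0.3 = 11.2, with df = 3 and (84−2) × 3 = 246. Power is 0.805 at N = 84 and 0.794 at N = 82, so 84 reproduces exactly.
- Between-group test on the average, λ = f²·N·m/(1+(m−1)ρ): this needs N = 612; power at 84 is 0.18.

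The powered test is therefore group-by-time.

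**2. Which four time points?** Change from baseline over three post-intervention points makes baseline plus three, which is four. Table 1 agrees. The parenthesis on week 52 does not: it suggests either four post-baseline visits (6, 16, 26, 52) or five points with baseline. Baseline plus weeks 6, 16 and 26 is the best-supported reading, but the text does not settle it.

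**3. What does the covariate do?** Take Y(i,t) = time + group × time + β·x(i) + patient + error. For any visit t, Y(i,t) − Y(i,0) contains no β·x(i). Simulated complete data sets (84 patients, ρ = .7) confirm this:

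| Covariate | F, none | F, main effect only | F, with covariate-by-time |
|---|---|---|---|
| Baseline outcome | 0.6252 | 0.6252 | 0.9486 |
| Another baseline variable | 0.8288 | 0.8288 | 0.7952 |

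In a mixed model on a further such data set, the group-by-time estimates (0.041, 0.210, 0.125) and their standard errors are the same with no covariate and with a main effect only. With baseline-by-time terms they become −0.038, 0.103 and 0.034, exactly the ANCOVA estimates at each visit.

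**4. Size of the leftover imbalance** (equal correlation .7, no treatment effect). A baseline difference just significant at N = 84 is 1.96 × √(4/84) = 0.43 SD. The expected spurious difference in change is (1 − 0.7) × 0.43 = 0.13 SD in favour of the arm that started worse. At N = 140 the figures are 0.33 and 0.10 SD.

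**5. Type I error by simulation.** Over 20,000 null trials at N = 84, the unadjusted test rejects in 5.2% of all trials. Among the 1,011 with a significant baseline difference it rejects in 126 (12.5%); with covariate-by-time terms it rejects in 52 (5.1%). Two larger runs (30,000 and 40,000 trials) gave 11.5% and 11.6% for the unadjusted test, and 5.2 to 5.7% for ANCOVA on the post-baseline scores.

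**6. Precision for the mean of three post-baseline visits** (SD = 1, ρ = .7).

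- Variance of the mean: (1 + 2 × 0.7)/3 = 0.80.
- Change from baseline: 0.80 + 1 − 2 × 0.7 = 0.40; SE = √(0.40 × 4/84) = 0.138.
- ANCOVA: 0.80 − 0.7² = 0.31; SE = √(0.31 × 4/84) = 0.121.
- Ratio 0.121/0.138 = 0.88, so the standard error is about 12% lower.

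**The case against.** - **The covariate form is not stated.** This stands. With covariate-by-time terms the model returns the ANCOVA estimates and the conditional error is about 5%. A reader might infer that the planned adjustment certainly does nothing; the text does not support that. What remains is that two models fitting the same sentence give different primary results. Detail may be left to an analysis plan, but the article itself states the model, the number of time points and the role of the covariates.
- **The week-52 remark may mean four post-baseline visits.** Baseline would then be only a covariate and this point would fall. That reading conflicts with the endpoint definition and Table 1. It also leaves the powered group-by-time test asking only whether the arm difference varies between follow-up visits, to which a constant benefit contributes nothing.
- **The identity needs complete data.** This stands. The plan recruits 140 for 84 and foresees maximum-likelihood handling of missing data. In one refit with an assumed 40% dropout (N = 140, ρ = .7), adding baseline as a main effect moved the last-visit term from 0.028 to 0.071 and its standard error from 0.150 to 0.141.
- **Not every covariate is constant.** This stands. Table 1 repeats MMSE at weeks 11 and 21 and records medication at many visits; covariates that vary over time do not cancel.
- **The test is valid overall.** This stands. The excess is about 0.05 × (12% − 5%) = 0.35% of null trials, and any change-score analysis behaves this way after an imbalance.

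A reader might also infer a large gain in power, from 80% to about 95%, for a constant effect of 0.46 SD at N = 84. That contrast mixes two things. A 1-df test of mean change without any covariate already reaches about 91% (0.46/0.138 = 3.3 standard errors), against about 96% for ANCOVA (0.46/0.121 = 3.8). Most of the gap comes from moving from 3 df to 1 df, so it should not be credited to the covariate.

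**Conclusion.** The point holds conditionally. If baseline is one of the four levels, covariates are measured once and enter as main effects, and data are complete, the stated adjustment cannot alter the group-by-time test or remove regression to the mean. The first condition is the best-supported reading; the second is left open.

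The consequence is limited to trials with a chance imbalance: about 11 to 12% rejection instead of about 5 to 6%, in roughly 1 null trial in 20, with type I error about 5% overall. These figures assume one constant correlation of .7, the only value the protocol gives. The sample size of 84 is not wrong on this account. The change is worth making because it delivers the baseline adjustment the plan intends and gains precision from data already collected.

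**What to change.** 1. State which visits enter the primary model, and reconcile the week-52 remark in the Sample size section with the Outcomes section and Table 1.
2. Take week 0 out of the outcome vector. Analyse IDDD at the post-intervention visits (weeks 6, 16 and 26 on the present endpoint definition) with baseline IDDD as a pre-specified covariate, whether or not it is imbalanced, together with its interaction with visit.
3. Report the COTP−COTC difference at each visit and averaged over visits.
4. Alternatively, keep week 0 as an outcome with the arm means constrained equal at baseline, and do not also use it as a covariate.

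The cost is analysis wording only: no new patients, visits or data.
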